### 4. Corneal Sensibility

Corneal sensibility is examined with esthesiometer in millimeters. Esthesiometer has a filament as long as 60 mm, the tip of the filament is softly touched to the cornea and blinking reflex is observed. Corneal sensibility is categorized into: normal (55-60 mm), mild hypoesthesia (50-54 mm), hypoesthesia (40-49 mm), severe hypoesthesia (30-39 mm), and very severe hypoesthesia (<30 mm).

### 5. Corneal Exposure

Corneal exposure is exposed corneal distance when eyes closed in millimeters.

## **Efficiency Outcomes:**

### 1. Safety of Surgery

Safety of surgery will be assessed with incidence of complications during and post-operative (bleeding, infection, granulation, implant extrusion, etc.).

### 2. Duration of Surgery

Duration of surgery in minutes from first incision until the procedure is done.

### 3. Cost of Surgery

Cost of tools and materials used for the surgery, laboratory examinations, and medications.

## e. Participant Timeline

### Time Schedule

Lagophthalmos distance and dry eyes assessments (OSDI questionnaire, TBUT, Schirmer test without anesthesia, Schirmer test with anesthesia), epitheliopathy, corneal sensibility, and corneal exposure will be assessed at 1 day, 7 days, 1 month, 3 months, and 1 year post-operatively. Complication and cost of surgery will be assessed intra-operative and post-operative until 1 year. Duration of surgery will be assessed during the surgery.

[figure not shown]

#### **f. Sample Size**

This study uses sample size calculation formula for two-tailed hypothesis test:

$$n = \frac{Sd^2 (Z_{1-\alpha/2} + Z_{1-\beta})^2}{(\mu_0 - \mu_a)^2}$$

$$n = 1,19^2 \frac{(1,96 + 0,842)^2}{1^2}$$
$$n = 12$$

n = total sample

Sd = standard deviation of mean difference (1.19)

$Z_{1-\alpha/2}$  = type 1 error (1.96)

$Z_{1-\beta}$  = type 2 error (0.842)

$\mu_0 - \mu_a$  = significant mean difference of both groups (1 mm represents significant)

Researcher determines sample size of minimum 12 eyes in each group.

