### Statistical Methods

Data will be analyzed using univariate, bivariate, and multivariate analysis. Univariate test is used to analyze frequency distribution of study variables. Bivariate test is used to analyze relation between two variables, using Independent T-Test, Wilcoxon, homogeneity test, and Mann-Whitney test. Multivariate test uses General Linear Model Repeated Measure with ANOVA. All tests using  $\alpha = 0.05$ .

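### The sample size formula for two randomised groups is the one-sample form and its SD of 1.19 is undefined; if that SD is within-group, 12 eyes per group gives about 50% power for 1 mm, not 80%

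*Protocol*

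**What the plan says.** Protocol section 2.f announces a two-sided test ("This study uses sample size calculation formula for two-tailed hypothesis test") and prints n = Sd²(Z₁₋α/2 + Z₁₋β)²/(μ₀ − μₐ)². The z-values are entered as "type 1 error (1.96)" and "type 2 error (0.842)". The effect is described as the "significant mean difference of both groups (1 mm represents significant)". Sd is 1.19, which the legend attaches to a mean difference without saying which difference, and no source is given. The legend defines n as follows: "n = total sample". The section then closes with: "Researcher determines sample size of minimum 12 eyes in each group".

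Section 2.g (Recruitment) adds 20% for drop-out. Section 2.h (Assignment of Interventions) randomises between the two techniques in blocks of 2, which implies 1:1 allocation. Statistical Methods in section 3 lists the two-variable tests: "using Independent T-Test, Wilcoxon, homogeneity test, and Mann-Whitney test".

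**The concern.** The printed formula contains one variance term. That suits one mean tested against a fixed value, or a set of paired differences. This trial randomises to two groups, states its effect as a difference between them, and lists an independent-samples t-test. The variance of a difference between two independent means is the sum of two terms, so with a within-group SD the number per group is twice what the printed formula gives.

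The section also contradicts itself on what 12 counts. The legend makes it the whole trial, while the closing sentence makes it one of two groups, that is 24 eyes.

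This calculation is the only justification given for the size of the trial. If the factor of 2 is missing, the trial has roughly an even chance of missing the 1 mm difference that the protocol itself treats as important, while its stated inputs imply a four-in-five chance of detecting it.

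**Working it through.** **Inputs, all from section 2.f unless noted.** Two-sided α = 0.05 (z = 1.96). Power 80%, implied by z = 0.842 although the percentage is not written out. δ = 1 mm between groups. Sd = 1.19, with mm assumed. Twelve eyes per group. Section 2.g adds 20%: 12 × 1.2 = 14.4, so 15 per group.

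**Step 1: reproduce the plan's figure.**

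n = 1.19² × (1.96 + 0.842)² / 1² = 1.4161 × 7.8512 = 11.12, rounded up to 12.

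The arithmetic is right for the formula printed. The question is whether that formula fits the design.

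**Step 2: two-group formula, taking 1.19 as the within-group SD.**

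n per group = 2 × SD² × (Z₁₋α/2 + Z₁₋β)² / δ² = 2 × 11.12 = 22.24, so 23 per group. By exact t-test power, 23 per group gives 79.6% and 24 gives 81.3%, so the requirement is 23 to 24 per group.

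**Step 3: power at the planned size on the same reading.**

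Standard error of the difference at 12 per group = 1.19 × √(2/12) = 0.486. Then δ/SE = 1/0.486 = 2.058.

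- Normal approximation: Φ(2.058 − 1.96) = 53.9%.
- Independent t-test (noncentral t, 22 df): 50.3%.

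The same SD applies whether it describes the outcome itself or its pre-post change within a group. Comparing change between two groups still needs the factor of 2.

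| Eyes per group | Power for 1 mm, t-test | Power for 1 mm, normal | Difference with 80% power, t-test |
|---|---|---|---|
| 12 | 50.3% | 53.9% | 1.42 mm |
| 15 (20% added, no losses) | 60.3% | 63.4% | 1.26 mm |
| 23 | 79.6% | 81.3% | – |
| 24 | 81.3% | 82.9% | – |

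**Step 4: the other reading of 1.19.**

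Suppose 1.19 is the SD of the difference between two independent eyes, one from each group. Then Sd² = 2σ², so σ = 1.19/√2 = 0.84 per eye, and Sd²(Z + Z)²/δ² = 2σ²(Z + Z)²/δ². The printed formula is then the two-group formula for the number per group. At 12 per group, power is 79.4% (t-test) or 82.9% (normal).

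**Step 5: which reading does the section support?**

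It settles neither. The legend's phrase for Sd fits a pre-post change within a group as well as a difference between eyes. The legend's definition of n as a total does not fit Step 4, where n is a number per group. The closing sentence, 12 in each group, does fit it.

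**The case against.** The strongest reply is that the protocol never calls 1.19 a within-group SD. It ties Sd to a mean difference and describes the effect as the "significant mean difference of both groups". Read together, those lines can mean a between-group difference SD. On that reading the formula is correct per group, the closing sentence is correct, and power is close to the intended 80%. This stands as far as it goes. It rules out stating 50% without a condition, but it does not rescue the section, which neither states that reading nor gives a source, and which labels n in a way that conflicts with it.

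A second reply is that 12 is a minimum and that 20% is added. That is fair. On the within-group reading, however, even 15 per group with every eye analysed gives only about 60%.

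Two stronger inferences are tempting and are not supported. A reader might take the legend's label to mean that only 12 eyes, 6 per group, are planned. The closing sentence explicitly sets 12 in each group, so the label is a conflict of wording and does not reduce the trial's power. A reader might also infer that a non-significant result will be reported as showing no 1 mm difference. Nothing in the protocol says so: its hypothesis (section 1.c) is that modified tarsorrhaphy is superior, and it makes no claim of equivalence.

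**Conclusion.** The point holds in conditional form. As written, section 2.f sizes a two-group comparison with a one-sample or paired formula, leaves its SD undefined and unsourced, and gives two incompatible meanings to n.

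The size of the error depends on what 1.19 is. As a within-group SD, of the outcome or of its change, it leaves about 50% power for 1 mm at 12 per group where 80% is implied, and the requirement would be about double the planned number. As an SD of the difference between two independent eyes, it leaves about 79%, and the fault is confined to the missing definition and the label on n. The document does not establish either reading.

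The figures assume 1:1 allocation, a two-sided 5% independent t-test, the same SD in both groups, and independent eyes. Any correlation between fellow eyes of bilateral patients is a separate matter and is not counted here.

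**What to change.** In section 2.f:

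1. Print the two-group formula, n per group = 2 × SD² × (Z₁₋α/2 + Z₁₋β)² / δ², with SD defined as the within-group SD.
2. State what 1.19 is (outcome, pre-post change, or between-eye difference) and give its source.
3. Replace the legend's definition of n with the number per group.
4. Restate the power to match the answer to item 2:
   - If 1.19 is a within-group SD: 12 evaluable eyes per group gives about 50% power for 1 mm, or 80% power for about 1.4 mm (about 1.26 mm at 15 per group).
   - If 1.19 is the SD of the difference between two independent eyes: say so, enter 0.84 as the within-group SD, and state about 79% power for 1 mm at 12 per group.

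The power sentence should not be written until item 2 is answered, since the wrong choice would put a new error into the protocol. The cost is wording only, and the planned number can stay. The downside is that the stated power may be less favourable.

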#### **h. Assignment of Interventions**

##### Allocation Sequence Generation

This is a multicenter PROBE (Prospective Randomized Open-label, Blinded-Endpoint) clinical trial study. Research team members will assign treatment received on all sample with randomization using blocking restriction size of 2.

##### Allocation Concealment Mechanism

Each sample will be assigned a number to conceal allocated intervention.

## **3. DATA COLLECTION, MANAGEMENT, ANALYSIS**

### Data Collection Methods

Data will be collected by research team members (three oculoplastic surgeons with equal qualifications) from the first subject enrolment until last follow up. Data collection instruments include questionnaire, data log, and laboratory tests. Questionnaire and data log are attached in Appendix 2-6.

### Statistical Methods

Data will be analyzed using univariate, bivariate, and multivariate analysis. Univariate test is used to analyze frequency distribution of study variables. Bivariate test is used to analyze relation between two variables, using Independent T-Test, Wilcoxon, homogeneity test, and Mann-Whitney test. Multivariate test uses General Linear Model Repeated Measure with ANOVA. All tests using  $\alpha = 0.05$ .

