## **b. Objectives**

- Main objective

Comparing effectivity and efficiency between modified tarsorrhaphy and gold weight implant technique as operative treatment for paralytic lagophthalmos in leprosy patients

- Specific objectives

Assessing the success of modified tarsorrhaphy and gold weight implant techniques as reconstructive treatment for lagophthalmos in leprosy patients according to:

- a. Lagophthalmos distance pre- and post-operative
- b. Dry eyes assessments (subjective assessment with OSDI questionnaire and objective assessment with TBUT, Schirmer test without anesthesia and Schirmer test with anesthesia)
- c. Epitheliopathy
- d. Corneal exposure
- e. Corneal sensibility
- f. Complication intra-operative and post-operative, which are bleeding, infection, granulation, implant extrusion
- g. Duration of surgery
- h. Cost of surgery

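### The protocol names no baseline-adjusted comparison of the arms for lagophthalmos distance, although the pre-operative distance is part of its first specific objective

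*Protocol*

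**What the plan says.** Protocol, Objectives, makes "Lagophthalmos distance pre- and post-operative" the first item by which the success of the two techniques is judged.

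Protocol, Statistical Methods, gives the methods in two sentences. The first is "Bivariate test is used to analyze relation between two variables, using Independent T-Test, Wilcoxon, homogeneity test, and Mann-Whitney test". The second is "Multivariate test uses General Linear Model Repeated Measure with ANOVA". No covariate and no analysis of covariance appears. The section does not say whether the t-test and Mann-Whitney test use the post-operative value or the change. It also does not say whether the repeated-measures model takes the pre-operative value as one of its time levels.

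Protocol, Sample Size, sets at least 12 eyes per group for a 1 mm difference. It defines the spread as "Sd = standard deviation of mean difference (1.19", which does not settle whether 1.19 mm is the SD of the post-operative distance or of the change from baseline.

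Eligibility Criteria set no range for the pre-operative gap. Allocation Sequence Generation describes blocks of two and mentions no stratification by severity.

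**The concern.** Patients can enter with small or large gaps, and a larger gap before surgery plausibly goes with a larger residual gap afterwards. With about 12 eyes per arm, randomisation leaves some difference in starting severity. The listed methods can be read in several ways, and each has a drawback:

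- **Two-group test on post-operative values.** The pre-operative value is not used.
- **Two-group test on change scores.** A raw baseline difference is removed, but with more noise than regression on baseline. When the correlation is low, this can be worse than ignoring baseline.
- **Repeated-measures ANOVA with the pre-operative value as a time level.** The group-by-time term compares changes. The group main effect averages in a time point at which surgery has had no effect.
- **Wilcoxon test, if this means the signed-rank test before and after surgery within each arm.** It does not compare the arms.

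At stake is precision that the planned data would provide without recruiting anyone, in a trial too small to waste it.

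**Working it through.** **Inputs from the protocol (Sample Size).** Two-sided test, z = 1.96; power 80%, z = 0.842; SD 1.19 mm; target difference 1 mm; 12 eyes per group.

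**Assumptions, not in the protocol.** Baseline SD 1.19 mm, borrowed because no baseline SD is given. Correlation rho between pre- and post-operative distance of 0.3, 0.5 or 0.7. Equal SD at both times. Eyes independent.

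**1. The protocol's own figure.** 1.19² × (1.96 + 0.842)² / 1² = 11.12, rounded up to 12. This reproduces. It is the one-sample form; for two independent groups the variance doubles, 2 × 11.12 = 22.24, so 23 per group. At 12 per group the two-sample t-test (noncentral t, 22 df) has 50% power for 1 mm. That is a separate matter, but it is the starting point for the comparisons below.

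**2. Chance difference between arms before surgery.** SE = 1.19 × √(2/12) = 0.486 mm; 95% range ±1.96 × 0.486 = ±0.95 mm. The probability of 1 mm or more in either direction is about 4%. At assumed baseline SDs of 1.5, 2 or 3 mm it is 10%, 22% or 41%. With equal SDs, an imbalance moves the unadjusted estimate by rho times its size. At the edge of the 95% range with rho = 0.5 that is 0.5 × 0.95 = 0.48 mm.

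**3. Power if 1.19 is the post-operative SD.** The adjusted residual SD is 1.19 × √(1 − rho²) and the SD of change is 1.19 × √(2 − 2rho). The adjusted power uses 21 df and inflates the variance by 1 + 1/20 = 1.05 for estimating the baseline slope.

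| rho | Variance removed (rho²) | Adjusted SD | Power, adjusted | SD of change | Power, change score | Power, post-operative value |
|---|---|---|---|---|---|---|
| 0.3 | 9% | 1.135 | 52% | 1.408 | 38% | 50% |
| 0.5 | 25% | 1.031 | 60% | 1.190 | 50% | 50% |
| 0.7 | 49% | 0.850 | 77% | 0.922 | 72% | 50% |

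**4. Power if 1.19 is the SD of change.** The adjusted SD is 1.19 × √((1 + rho)/2) and the implied post-operative SD is 1.19 / √(2 − 2rho).

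| rho | Adjusted SD | Power, adjusted | Power, change score | Post-operative SD | Power, post-operative value |
|---|---|---|---|---|---|
| 0.3 | 0.959 | 66% | 50% | 1.006 | 64% |
| 0.5 | 1.031 | 60% | 50% | 1.190 | 50% |
| 0.7 | 1.097 | 55% | 50% | 1.536 | 33% |

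In every row of both tables the adjusted analysis has the highest power, although at rho = 0.3 its lead over the post-operative comparison is only about 2 points.

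**5. Dilution of the group main effect.** Participant Timeline lists five post-operative visits. With the pre-operative value as a sixth level, a constant effect d averages to (5 × d + 0) / 6, so the main effect shrinks by one sixth.

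**The case against.** The strongest reply is that choosing covariates is ordinary SAP work, that the SAP is not shown, and that a short list of methods does not rule out adjustment. Part of this stands: silence is not exclusion. But the section does more than stay silent. It names the between-arm methods, describes the first set as two-variable tests and specifies the multivariable model as ANOVA. Naming a better model for data the trial already intends to use is a concrete improvement to stated text.

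A reader might infer more than the documents support:

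- **That no listed analysis can deal with baseline.** This goes too far. Change scores or the group-by-time term would remove a raw baseline difference, and the wording leaves both open.
- **That an imbalance as large as the 1 mm target is to be expected.** The protocol gives no baseline SD. With 1.19 mm borrowed, 1 mm or more occurs in about 4% of trials; it becomes common only at wider assumed spreads.
- **That the unadjusted comparison is invalid.** Under randomisation it is unbiased on average and keeps its type I error.
- **That the pre-operative measurement is not scheduled.** The timeline text lists only post-operative visits, but its figure is not shown and the post-operative evaluation forms are illegible, so nothing can be concluded.

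It is also true that the low starting power comes from the sample size formula and not from the missing covariate.

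**Conclusion.** The point holds as a recommendation on efficiency, not as an error that invalidates the planned comparison. Statistical Methods names no baseline-adjusted comparison of the arms and leaves open how the pre-operative distance is used, although that distance belongs to the first specific objective. The size of the gain depends on a correlation the protocol does not give and on which SD 1.19 mm represents. Relative to the post-operative comparison under the first reading, it runs from about 2 to 27 percentage points of power (50% to 52% or 77%). Relative to change scores under the second, it runs from about 5 to 16 (50% to 55% or 66%). The direction is the same under both readings across the correlations examined. Adjustment also protects against conditional bias if the arms turn out to differ before surgery. All power figures assume 12 independent eyes per arm; two eyes from one patient would change them.

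**What to change.** In Statistical Methods, make the main between-arm analysis of lagophthalmos distance a model of the post-operative distance on group plus pre-operative distance. This can be ANCOVA at the chosen visit, or the repeated-measures model fitted to the post-operative visits only, with the pre-operative value as a covariate and not as a time level. Use the same form for the other continuous outcomes that have a pre-operative value. Keep within-arm tests of pre- against post-operative values as description only.

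The change is one of wording: no extra patients, and no data beyond the pre-operative value the objective already calls for. It costs one degree of freedom per model. Adding hospital as a further covariate is not part of this recommendation: with three hospitals it would cost two more degrees of freedom in a very small trial, and the protocol gives no sign that hospital predicts the outcome.

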## **4. MONITORING**

Any complaints from subjects or adverse events will be informed to the principal investigator or research assistants (contact information is included in the informed consent form). Adverse events will be monitored during study period. Surgical complications will be treated by oculoplastic surgeon. Other complications will be referred to related specialists. Serious adverse events will be judged by research ethics committee.

## **5. ETHICS AND DISSEMINATION**

### **Research Ethics Approval**

This study will be submitted to Medical and Health Research Ethics Committee (MHREC) Faculty of Medicine, Public Health and Nursing Universitas Gadjah Mada - dr. Sardjito General Hospital, Yogyakarta, Indonesia for ethical approval.

### **Protocol Amendments**

Any changes of the protocol will be communicated to relevant parties (research assistants, research team members, investigators, regulators).

### **Consent**

Subjects must sign informed consent form as agreement for participating in this study.

### **Confidentiality**

Subject personal information and study outcomes will be collected and can only be accessed by the research assistants and principal investigator to maintain confidentiality. Data can only be accessed by permission from the principal investigator with prior agreements and not for commercial purposes.

### **Declaration of Interests**

This study is independent from sponsor. All research team members and investigators have no conflict of interest.

### **Ancillary and Post-Trial Care**

Any complaints from subject post-trial can be communicated to the principal investigator or research assistants (contact information is included in the informed consent form).

### **Dissemination Policy**

Investigator plans to submit the result of this study to relevant publication. Full protocol, participant-level dataset, and statistical code can only be accessed with permission and agreement with principal investigator.

## APPENDIX 2

### RESEARCH STATUS

|                            |   |                                                        |
|----------------------------|---|--------------------------------------------------------|
| Date of examination        | : |                                                        |
| Research serial number     | : |                                                        |
| Medical record number      | : |                                                        |
| Name                       | : |                                                        |
| Date of birth              | : | Age :                                                  |
| Address                    | : |                                                        |
|                            | : |                                                        |
| Phone number               | : |                                                        |
| Occupation                 | : | Marital status :                                       |
| Gender                     | : | M / F                                                  |
| Leprosy type               | : | PB / MB                                                |
| Duration of leprosy        | : |                                                        |
| Leprosy reaction           | : | No reaction / Type I Reaction / Type II Reaction       |
| MDT treatment              | : | not received yet / in therapy / release from treatment |
| Duration of MDT            | : |                                                        |
| Corticosteroid treatment   | : | yes / no                                               |
| Duration of corticosteroid | : |                                                        |
| Disability                 | : | none / grade 1 / grade 2                               |

## APPENDIX 4

